#### Data analysis

The software SPSS [Statistical Package for Social Sciences (SPSS Inc., Chicago, IL, EUA)], version 22.0, will be used for the statistical analyses. Descriptive statistics will be calculated and tabulated to characterize the participants. For the comparisons of the two means, Student’s *t* tests will be used to compare groups in terms of the quantitative variables that have Gaussian distributions, and the non-parametric Mann-Whitney test will be used to compare groups in terms of the quantitative variables that do not have Gaussian distributions. The qualitative variables will be described as counts and frequencies.

A general linear model (parametric) will be used to compare groups in terms of the quantitative variables that represent the differences between the baseline and post-intervention points, and when it is not possible to use a general linear model, the non-parametric Wilcoxon paired test will be used to compare the quantitative differences between the baseline and post-intervention points in each group separately. The quantitative variables will be described as mean, standard deviation, median, minimum and maximum values, and the number of valid observations (*n*).

The chi-square test (or Fisher’s exact test or the likelihood ratio) will be used to compare the qualitative variables between groups. The generalized estimating equation model will be used to compare groups in terms of the qualitative differences between the baseline and post-intervention time points. When it is not possible to use a generalized estimation model, the non-parametric McNemar test will be used to compare the qualitative differences between the baseline and post-intervention time points in each group separately. The level of significance will be 5% (*p* value < 0.05) for each of the comparisons.

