### Randomization procedures

The participants will be randomly assigned to either the experimental group or the control group. The allocation sequence will be generated by a research assistant ([name]) using a computer-generated random number table with a group ratio of 1:1 and will be concealed in sequentially numbered, sealed, and opaque envelopes. The envelopes will be kept in a closed locker at the centre to which only the research assistant will have access. The envelopes will be given to the PT ([name]) immediately prior to the first outpatient session.

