### Statistical analysis and sample size calculation

#### Calculation of the sample size

A sample size calculation was performed to estimate the number of participants needed to obtain a statistical power of 0.80 at an alpha level of 0.05. A pilot study was previously conducted to calculate the sample size (unpublished). The results of this study showed improvements in the fast-twitch muscle fibres in both groups after the intervention. In the experimental group, the mean number of fast-twitch muscle fibres was 1.2 (± 0.7), and in the control group, it was 1.1 (± 1.7). Based on these results, we used Student’s bilateral *t* test to calculate the sample size, which was a minimum of 72 participants per group. To estimate the sample loss during the study, loss percentages from 0 to 20% were assumed. For each patient that is expected to terminate their participation in the study, two new patients will be included. Thus, considering a loss of 20%, the sample size was a minimum of 86 patients in each group.

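### The named t test and general linear model pool the variance by default although the pilot spreads differ 2.4-fold; an unequal-variance version is a cheap safeguard if final group sizes differ

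*Protocol article*

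**What the plan says.** All references are to the protocol article.

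- **Data analysis, two-group comparison.** Student's t "tests will be used to compare groups in terms of the quantitative variables that have Gaussian distributions". Mann-Whitney is named for variables that are not Gaussian.
- **Data analysis, change from baseline.** "A general linear model (parametric) will be used to compare groups in terms of the quantitative variables that represent the differences between" baseline and post-intervention. No variance structure is given for the t test or the model, and no unequal-variance version is mentioned. "The level of significance will be 5"% for each comparison.
- **Calculation of the sample size.** "In the experimental group, the mean number of fast-twitch muscle fibres was 1.2", printed with ± 0.7. The control value is 1.1 with ± 1.7. The trial is sized with a two-sided Student's t test at 72 per group, raised to 86 for a loss of up to 20%.
- **Randomization procedures.** Allocation uses a "computer-generated random number table with a group ratio of 1:1". No blocking is described.
- **Interventions.** Intention-to-treat analysis is invoked only if dropout exceeds 15%.

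**The concern.** A pooled-variance test weights the two sample variances by their degrees of freedom. With equal group sizes the pooled and unpooled standard errors coincide, so unequal variances do little harm. With unequal sizes they separate. If the more variable group is the smaller one, the pooled standard error is too small and the test rejects too often. If it is the larger one, the standard error is too large and power is lost.

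The plan's own pilot suggests that the control group is much the more variable. Several features could leave the analysed groups unequal:

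- no blocking is described;
- losses of up to 20% are allowed for, and each expected loss is replaced by two new patients, with nothing said about keeping the arms balanced;
- below 15% dropout, the plan does not commit to analysing everyone randomised;
- participants know their group, and only one group has palpation as treatment.

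At stake is whether the nominal 5% level for the main comparison of means is the true one.

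**Working it through.** **Inputs.** From Calculation of the sample size: experimental ± 0.7 and control ± 1.7, read as standard deviations (an assumption, since the article does not define ±); 72 per group, 86 after loss; "statistical power of 0.80 at an alpha level of 0.05"; two-sided test. Data are assumed normal with equal means.

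**The plan's own figure.** The pooled SD is √[(0.7² + 1.7²)/2] = √1.69 = 1.30. For a difference of 1.2 − 1.1 = 0.1, n per group = 2 × (1.96 + 0.8416)² × 1.69 / 0.1² ≈ 2,653. The stated 72 is not reproduced. That is a separate matter, but it limits how far the printed pilot values can be trusted here. The 86 is 72 × 1.2 = 86.4, rounded down.

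**Spread.** SD ratio 1.7/0.7 = 2.43; variance ratio 2.89/0.49 = 5.9.

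**Standard errors.** True: √(0.49/n_E + 2.89/n_C). Pooled: √{[(n_E − 1)0.49 + (n_C − 1)2.89]/(n_E + n_C − 2) × (1/n_E + 1/n_C)}.

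- *86/86.* True variance (0.49 + 2.89)/86 = 0.03930; pooled variance 1.69 × 2/86 = 0.03930. Ratio of standard errors 1.00.
- *86 experimental / 69 control* (86 × 0.8 = 68.8). True: 0.49/86 + 2.89/69 = 0.04758, standard error 0.2181. Pooled: (85 × 0.49 + 68 × 2.89)/153 = 1.5567; × 0.026121 = 0.04066, standard error 0.2016. Ratio 0.924, so 7.6% too small.
- *69 experimental / 86 control.* True: 0.49/69 + 2.89/86 = 0.04071, standard error 0.2018. Pooled: (68 × 0.49 + 85 × 2.89)/153 = 1.8233; × 0.026121 = 0.04763, standard error 0.2182. Ratio 1.082, so 8.2% too large.

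**Error rate.** The large-sample approximation is 2 × [1 − Φ(c × ratio)], with c the t critical value. Two simulation runs, of 200,000 and 400,000 trials per pair of sizes, check it.

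| Experimental / control | Approximation | Student, simulated | Welch, simulated |
|---|---|---|---|
| 86 / 86 | 4.8% | 5.1% | 5.0–5.1% |
| 86 / 77 (10% lost, control only) | 5.8% | 6.0–6.1% | 5.0–5.1% |
| 77 / 86 (10% lost, experimental only) | 4.0% | 4.2–4.3% | 5.0–5.1% |
| 86 / 69 (20% lost, control only) | 6.8% | 7.1% | 5.0–5.1% |
| 69 / 86 (20% lost, experimental only) | 3.3% | 3.5% | 5.0–5.1% |

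**If allocation is simple** (an assumption; the article may condense the method), the 95% range for one arm out of 172 is 73 to 99. The Student error is 7.9% at 99/73 and 3.0% at 73/99. Averaged over all splits it is about 4.9% by the approximation.

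**The case against.** The case for leaving the text alone is substantial.

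- **The variance form is not written down.** The article does not say equal variances, and pooled versus Welch is often settled in an analysis plan that is not shown. This stands as a limit: a reader might infer that the plan has expressly chosen the equal-variance test, and it has not. But it does name methods whose usual form pools, and someone following the text would run that form.
- **The planned sizes are equal.** The 20% allowance covers both groups, and nothing forecasts one-sided loss. This stands, and it makes the effect conditional.
- **The direction is uncertain.** If palpation drives women out, the low-spread group shrinks and the test becomes conservative. Women who cannot tolerate the examination are excluded, and controls are offered the palpation protocol after four weeks, which gives them a reason to stay. A reader might infer that false positives will be inflated; the document gives that direction less support than the other.
- **The outcome may not reach the t test.** It is a count from 0 to 10, and the plan's own rule may send it to Mann-Whitney. This stands, so the figures apply only where means are compared parametrically. Mann-Whitney does not fully avoid the issue: as a test of location it also assumes equal spread.
- **The null is narrow.** If palpation changed nothing, both randomised groups would share one distribution and one variance. The problem needs equal means with unequal variances. The pilot pattern (1.2 against 1.1, with very different spreads) is of that kind, but it comes from an unpublished study of unstated size.

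**Conclusion.** The point holds as a minor one. The named methods pool the variance by default, and the plan's own pilot suggests markedly unequal variances. At the planned equal sizes the error rate is sound, at about 5.1%. With unequal final sizes it can depart from 5% in either direction: about 4.2% to 6.1% for 10% loss in one arm only, and 3.5% to 7.1% for 20% loss in one arm only. These figures rest on ± being a standard deviation, on the pilot spreads holding in the trial, and on normal data.

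Two stronger readings are not supported. One is that the 5% level is wrong as designed; it is not at 1:1. The other is that the trial's confidence interval is wrong; the article plans no confidence interval, so there is no text for that to apply to.

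**What to change.** In Data analysis, state that where two means are compared parametrically the Welch (unequal-variance) t test will be used, and that the group effect in the general linear model will be tested with heteroscedasticity-robust standard errors (for example HC3). Apply this in every case rather than after a preliminary test of variances. Confirm that the software version named in the article offers the robust option. If it does not, a Welch test on the change scores gives the corresponding unadjusted two-group comparison.

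The cost is one sentence of wording and, if the variances turn out equal, a negligible loss of degrees of freedom. No change to sample size, allocation or data collection is needed for this point.

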## Objectives and hypothesis

The specific objectives are to compare the experimental group (verbal instructions + body awareness techniques + vaginal palpation) and the control group (verbal instructions + body awareness techniques) with regard to the following factors:
The number of fast-twitch muscle fibres, as determined by the number of effective contractions (fast contractions with maximal force lasting 1 s each) out of ten contractions performed [11], before and immediately after the intervention;PFM function (voluntary contraction of the PFMs) and muscular endurance (duration of the muscular contractions in seconds), as measured by the Oxford scale [11], before and immediately after the intervention;The occurrence of associated contractions of the abdominal, gluteal, and adductor muscles during the voluntary contraction of the PFMs before and immediately after the intervention; andSelf-efficacy, before and immediately after the intervention, as measured by the self-efficacy scale for the practice of pelvic floor exercises [12].

The hypothesis of the present study is that the experimental group (verbal instructions + body awareness techniques + vaginal palpation) will have significantly more effective fast phasic fibres (contractions assessed by digital palpation) than will the control group after undergoing the interventions, as determined by the primary outcome.

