#### Primary outcome measure

##### Vaginal palpation and visual observation: phasic fibres

The patients will be in the lithotomy position when the phasic fibres of the PFMs are evaluated; they will have their hips and knees semi-flexed and rotated externally and their upper limbs placed to the sides of the trunk. They will be asked to contract their PFMs by raising the pelvic floor musculature towards the pubic symphysis.

The patients will be instructed to perform the contractions quickly and with the maximum possible force 10 times [11]. The number of fast-twitch contractions will be determined by calculating the number of effective contractions (fast-twitch contractions with maximal force lasting 1 s each) out of 10 contractions performed.

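### The plan does not fix one test for the primary count: a comparison framed on means can become a Mann-Whitney test, which does not test means and can reject when the means are equal

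*Protocol article*

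**What the plan says.** The primary outcome is obtained by "calculating the number of effective contractions (fast-twitch contractions with maximal force lasting 1 s each) out of 10 contractions performed" (Primary outcome measure), so it is an integer from 0 to 10. The hypothesis is that the experimental group "will have significantly more effective fast phasic fibres (contractions assessed by digital palpation) than will the control group after undergoing the interventions" (Objectives and hypothesis). The list of objectives in the same section speaks of the count before and immediately after the intervention.

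The sample-size section works with means. The pilot result is that "the mean number of fast-twitch muscle fibres was 1.2 (± 0.7), and in the control group, it was 1.1 (± 1.7" in parentheses, and the authors state that "we used Student’s bilateral *t* test to calculate the sample size".

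The Data analysis section then gives two rules that could each apply to this count:

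- **Two-group comparison of a quantitative variable.** It is introduced as a comparison of two means. Student's t is used if the variable is Gaussian; otherwise "the non-parametric Mann-Whitney test will be used to compare groups in terms of the quantitative variables that do not have Gaussian distributions".
- **Baseline-to-post differences.** A general linear model compares the groups. If it cannot be used, paired Wilcoxon tests are done within each group.

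Neither rule is tied to the primary outcome by name.

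**The concern.** The choice between Student's t and Mann-Whitney depends on the observed distribution, and the two tests do not ask the same question. Student's t asks whether the mean counts differ. The Mann-Whitney reference distribution assumes that the two groups have identical distributions, and the test responds to P(experimental > control) plus half of the ties. It stands in for a comparison of means only if the groups differ by a shift with the same shape. The article states no such condition, and its own pilot spreads are far apart.

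At stake is the meaning of a positive result. A significant Mann-Whitney test could be reported as palpation giving a larger mean number of effective contractions when the mean is the same in both groups. The hypothesis tested would also have been settled only after looking at the outcome.

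**Working it through.** **Inputs.** Pilot 1.2 (± 0.7) and 1.1 (± 1.7), with ± taken as SD because the text does not label it; 72 per group, or 86 with allowance for loss; two-sided 5% (all from Calculation of the sample size). Scale 0 to 10 (Primary outcome measure).

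**The plan's own figure.** With a difference of 1.2 − 1.1 = 0.1 and SD √((0.7² + 1.7²)/2) = √1.69 = 1.30, a two-sided t test at 80% power needs about 2 × (1.960 + 0.842)² × 1.69 / 0.1² ≈ 2,653 per group, not 72. The 86 matches 72 × 1.2 = 86.4. That is a separate matter. Here 72 and 86 serve only as the group sizes in the check.

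**Step 1: would the switch operate?** Counts were simulated on 0-10 with the least structured (maximum-entropy) shape that matches the pilot mean and SDs. A Shapiro-Wilk test rejected normality in 100% of samples of 72 in both arms. The article does not say how Gaussian shape is judged, but a move to Mann-Whitney is the likely result.

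**Step 2: can the shapes be alike?** The variance ratio is 1.7²/0.7² = 2.89/0.49 = 5.9. For a variable that cannot fall below 0, with mean m and SD s, (E X²)² ≤ E X × E X³, so skewness is at least s/m − m/s. For the control figures this is 1.7/1.1 − 1.1/1.7 = 1.545 − 0.647 = 0.90. If the figures are counts, the control arm must therefore be right-skewed, whatever shape is assumed.

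**Step 3: what does Mann-Whitney respond to?** With maximum-entropy counts and a common mean of 1.1, P(experimental > control) plus half of the ties is 0.609, not 0.50. Ignoring ties, the expected z is 0.109 / √((2n + 1)/(12n²)). At n = 72 this is 0.109/0.0483 = 2.26, and at n = 86 it is 0.109/0.0442 = 2.47. Both exceed 1.96, so more than half of trials should reject.

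**Step 4: simulation with equal means**, SDs 0.7 and 1.7, 10,000 trials per setting, tie-corrected Mann-Whitney:

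| Control-arm shape | Common mean | Rejects, n = 72 | Rejects, n = 86 |
|---|---|---|---|
| Maximum-entropy | 1.1 | 66.3% | 74.0% |
| Maximum-entropy | 1.15 | 64.0% | 71.8% |
| Maximum-entropy | 1.2 | 62.2% | 68.6% |
| Beta-binomial | 1.1 | 71.3% | 78.8% |
| Beta-binomial | 1.15 | 68.1% | 75.3% |
| Beta-binomial | 1.2 | 64.8% | 71.9% |

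Student's and Welch's t tests on the same data rejected in 5.4-6.3%. In a further 4,000 trials at common mean 1.15, every Mann-Whitney rejection favoured the experimental arm.

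**Step 5: how far does this depend on the assumptions?**

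- Symmetric integer change scores with the pilot SDs: 6-7%.
- Same distribution in both arms: 5.4%.
- Milder spread contrasts (common mean 1.15, n = 72 / 86): SDs 0.8 and 1.5 give 36% / 41%; 0.9 and 1.4 give 21% / 24%; 1.0 and 1.3 give 10% / 12%.
- Pilot SDs with the common mean elsewhere on the scale (n = 72): 6.8% at mean 3, 5.9% at mean 5 and 18.4% at mean 8. At mean 8 the probability in Step 3 is 0.454, so the tilt is then towards the control arm.

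**The case against.** The strongest reply is that the Mann-Whitney rule may not govern the primary outcome at all. The objectives speak of before and after, assessments are at baseline and after four weeks, and the Data analysis section has a general linear model for such differences. This stands in part. The hypothesis is worded as a comparison after the interventions, and the article does not say which route is primary. Neither reading can be treated as established.

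Second, the sentence before the pilot figures speaks of improvements in both groups, so 1.2 and 1.1 may be mean changes. This stands: on roughly symmetric changes the excess is small. The pilot is also unpublished, of unstated size, and does not reproduce the sample size, so its SDs are weak evidence.

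Third, a reader might infer from the 60-75% that the trial would falsely declare palpation effective that often when it does nothing. The documents do not support that. If palpation has no effect at all, the arms share one distribution and Mann-Whitney holds its level. The simulated arms do differ, in spread and shape, and rejecting equality of distributions there is correct. What would be wrong is reading that rejection as a difference in means.

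Fourth, choosing t or Mann-Whitney by distribution is conventional, and the hypothesis names no mean. But the rule itself is introduced as one about means and the trial is sized on means, so a rank test changes the question. Reporting means and medians alongside would reveal the mismatch but would not settle which result counts.

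**Conclusion.** The point holds in limited form. The Data analysis section leaves two possible routes for the primary count, and one of them changes the hypothesis according to the observed distribution. On that route Mann-Whitney does not test the difference in means on which the trial is framed and sized.

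The size is conditional. It is about 60-75% rejection at equal means with maximum-entropy counts (up to 79% with a beta-binomial control arm), in favour of the experimental arm. That requires the Mann-Whitney route, post-intervention counts with means near 1, and ± values that are SDs and carry over to the trial. With symmetric change scores it is 6-7%, and with no effect of any kind about 5%. The documents do not settle which case applies, so no single error rate can be attached to the trial.

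**What to change.** For the primary outcome, remove the switch based on Gaussian shape and name one between-group comparison of means in advance. The natural choice is the general linear model already in the Data analysis section, with the post-intervention count as response, the baseline count as covariate and heteroscedasticity-robust standard errors. Welch's t test is an acceptable alternative. Report the difference in mean number of effective contractions with a 95% CI. If the linear model is chosen, say that the within-group Wilcoxon fallback does not replace it for this outcome.

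Keep Mann-Whitney only as a supplementary analysis, described as a test of P(experimental > control).

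The cost is one or two sentences, with no new patients or data. The article says that protocol changes will be recorded in the registry, and this one should be recorded before outcomes are seen by group. The downside is some loss of power against a pure shift in a heavy-tailed outcome, where a rank test is more efficient.

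### The fallback for the change-from-baseline analysis tests each group separately, so it cannot answer the between-group objectives

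*Protocol article*

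**What the plan says.** The Objectives and hypothesis section is comparative throughout. It opens with "The specific objectives are to compare the experimental group" against the control group, before and immediately after the intervention. The hypothesis is that the experimental group "will have significantly more effective fast phasic fibres (contractions assessed by digital palpation) than will the control group after undergoing the interventions". The primary outcome is a count of effective contractions "out of 10 contractions performed".

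The Data analysis section sets two first-line analyses of change, both between groups:

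- Quantitative: "A general linear model (parametric) will be used to compare groups in terms of the quantitative variables that represent the differences between the baseline" and the post-intervention assessment.
- Qualitative: "The generalized estimating equation model will be used to compare groups in terms of the qualitative differences between the baseline and post-intervention time points".

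Each has a substitute for when the model cannot be used:

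- Quantitative: "the non-parametric Wilcoxon paired test will be used to compare the quantitative differences between the baseline and post-intervention points in each group separately".
- Qualitative: "the non-parametric McNemar test will be used to compare the qualitative differences between the baseline and post-intervention time points in each group separately".

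The same section also names between-group tests: Mann-Whitney for quantitative variables that are not Gaussian, and chi-square, Fisher's exact or likelihood ratio tests for qualitative variables. It does not say which endpoint or time point these cover, or whether they apply to change scores. Every comparison is tested at 5%.

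**The concern.** A paired test within one arm has as its null hypothesis that this arm did not change. Two such tests, one per arm, contain no test of the difference between arms. The switch from the first-line model to the fallback therefore changes the question as well as the method.

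This matters here because both arms are trained. The control group receives verbal instruction and body awareness work, and the sample size section reports that both groups improved in the pilot. The trial has to isolate what vaginal palpation adds to an active programme. Improvement within each arm does not show that, and neither does a comparison of two within-arm p values.

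**Working it through.** **1. The passages side by side.**

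| Element | Contrast addressed |
|---|---|
| Objectives and hypothesis | experimental v control |
| Linear model / GEE on change | experimental v control |
| Wilcoxon paired / McNemar fallback | post v baseline, one arm at a time |
| Mann-Whitney, chi-square/Fisher | between groups, but time point and variable not stated |

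Only the third row leaves the trial's question. The finding follows from this table alone; the figures below show what the fallback would deliver if it were used.

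**2. Inputs.** From the sample size section: 72 per group before loss, two-sided alpha 0.05, pilot 1.2 (SD 0.7) experimental and 1.1 (SD 1.7) control. The protocol gives no operating figure for the fallback, so there is none to reproduce. The 72 is used only as the stated number per arm. It does not itself follow from the pilot figures: a difference of 0.1 with SD √((0.7² + 1.7²)/2) = 1.30 needs 2,653 per group. That is a separate matter and does not bear on this point.

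**3. If the pilot values are changes (the article does not say).** Within-arm statistic = mean/SD × √n.

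- Experimental: 1.2/0.7 × √72 = 14.5
- Control: 1.1/1.7 × √72 = 5.5

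Power is about 100% in both arms. In a simulation of 4,000 trials (normal changes rounded to integers), separate Wilcoxon tests were significant in both arms in 99.9% of trials at the pilot values. With SD 1.30 in each arm, they were significant in both arms in 100% of trials when the true changes were equal (1.1 and 1.1), and also in 100% when they differed by 0.6 (1.7 and 1.1). The fallback cannot tell these two situations apart.

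**4. If the true changes are equal and smaller (assumed).** Let p be the power of the paired test in one arm, taken from the paired t test as an approximation. The arms are independent, so P(exactly one arm significant) = 2p(1 − p), and half of that is experimental only.

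| Equal true change | p at n = 72 | exactly one arm |
|---|---|---|
| 0.10 SD | 0.13 | 0.23 |
| 0.24 SD | 0.52 | 0.50 |
| 0.30 SD | 0.71 | 0.41 |

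The maximum of 2p(1 − p) is 0.50, at p = 0.5, so 0.24 SD is close to the worst case. A simulation with Wilcoxon tests, SD 1.30 and an equal change of 0.3 agrees: 26% experimental only plus 24% control only = 50%. With the pilot's unequal SDs (0.7 and 1.7) and an equal mean change of 0.3, experimental-only significance occurred in 64% of trials, because the less variable arm reaches significance more easily.

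**5. A between-group replacement under the same conditions.** Mann-Whitney on the change scores rejected in 4.5% to 5.2% of trials under equal change with equal SDs, and in about 6% with the pilot's unequal SDs. For an assumed true difference of 0.6 (SD 1.30) it rejected in 74%.

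**The case against.** The strongest reply is that the plan already holds between-group non-parametric tests. The hypothesis speaks of the state after the interventions and can be read as a comparison of post-intervention values. In a 1:1 randomized trial, Mann-Whitney on those values is a valid test of it. This stands in part. A reader might infer that a failed model would leave the primary hypothesis with no valid test at all, and the document does not support that. What remains is that these tests are not linked to the fallback, a time point or the change scores, and the only substitute prescribed for change is within-arm.

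A reader might also infer that the fallback is likely for the primary outcome, because a 0 to 10 count with a control SD (1.7) above its mean (1.1) looks skewed. This is not shown either. The trigger is only that the model cannot be used; failed assumptions are a natural reading but are not stated. If the pilot values are changes, they can be negative and no skew follows. If they are counts, skew need not disable the model: in simulated counts bounded at 0 and 10 with mean about 1.1 and SD about 1.7 (negative binomial shape assumed), the two-sample t test had type I error of 5.1% at 72 per arm and 4.9% at 86.

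Finally, nothing in the article says that significance in one arm only would be taken as a palpation effect. The 23% to 50% range is an error rate only under that unwritten reading, and it rests on assumed effect sizes.

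**Conclusion.** The point holds in a limited form. The Wilcoxon and McNemar fallbacks do not compare the groups and so cannot serve the comparative objectives. This is a stated rule that answers the wrong question, not a detail left to an analysis plan. It affects the substitute analysis of change only: the first-line models are between-group, and the McNemar branch concerns qualitative variables, so it does not touch the primary count.

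The practical consequence depends on what the pilot figures are. If they are changes, the fallback would be uninformative rather than prone to false positives, since both arms would be significant almost always. The one-arm-only pattern arises for smaller changes, and the percentages given for it are illustrations, not forecasts for this trial. The document gives no basis for a probability that the fallback will be invoked. Severity: should-fix.

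**What to change.** Replace the two fallback clauses in the Data analysis section with between-group analyses, and state that within-arm changes are reported as description without inferential weight.

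- **Quantitative outcomes:** for example, Mann-Whitney on the change scores, which is already named in the plan and only needs tying to this use. Alternatively, a baseline-adjusted between-group analysis with permutation or bootstrap inference.
- **Binary outcomes, such as associated muscle contractions:** between-group logistic regression of post-intervention status adjusted for baseline status, or Fisher's exact test at T5.

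The cost is two sentences, with no new data and no added participants. The Trial status section reports 165 of 172 participants recruited, so the wording should be settled and recorded before the blinded analysts receive the data.
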